### Design

This study will be conducted with multiple single-case design with four multiple randomized baselines, where the shortest baseline has two assessments and the largest has five, and the intervention phase has 18 assessments across time. We have recruited 40 students with intellectual disabilities who require AAC.

To evaluate the effectiveness of the intervention effects in this study, the What Works Clearinghouse (WWC) single-case design technical documentation provides appropriate study analysis techniques [20]. Andzik and Chung [8] recommend that researchers follow these quality guidelines for single-case experimental studies to ensure internal validity of the study with reliable measures (Fig. 1).

**Fig. 1 Fig1:**
[figure not shown]
Assessments to be administered. This trial protocol is in line with standard protocol items: Recommendations for Interventional Trials (SPIRIT) 2013. Standard Protocol Items: Recommendations for Interventional Trials (SPIRIT) figure with timeline for recruitment, assessments, and interventions. Black lines indicate “conducted every month,” and X indicate “only conducted three times across 18 months, i.e., month 1, 12, and 18.” A, B, C, and D indicate the four randomized groups and when they start the reading intervention

### Sample size calculation and power

The power calculation is based on Hedges et al. [31] where the input parameters are as follows:Number the phases is equal to one (i.e., we have one baseline phase and one intervention phase)Intraclass coefficient correlation of 0.5Autoregressive effect 0.5Alpha error probability of 0.016 (giving we have three primary outcomes)Minimum number of observations per phase is threeMinimum detectable effect size is a Cohen’s *d* of 0.5

Under those input parameters, our power is 75.84%; however, it is important to note that our study has an unbalanced design (different amounts of observations per phase resulting in the intervention phase being larger than the baseline). This is designed specifically to improve the adherence of the students and their families on the study. In our experience, being without intervention for more than 6 months (e.g., baseline phase) would reduce the interest and adherence of the participants in the trial. Therefore, our observable power will be superior than the above reported. The estimation of the power was conducted using the Power Analysis and Sample Size software (PASS) [32].

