#### Assessment of the outcomes

A registration form has been developed to use during the assessment and data collection of outcomes. The form is designed so the teacher can click whether the student answers options 1, 2, 3, or 4. It is the student’s teacher who will carry out all the tests. The teacher must register correct or incorrect responses during the assessment. Only the teacher and the student will be present during the testing, and all test situations will be filmed. Each student will receive an individual follow-up plan that will describe in detail when tests will be carried out and when the intervention will start. Within each phase, 20% of the recorded films will be randomly selected and evaluated by two external raters at item-level across the five primary outcomes. Agreement between the two raters and the teachers will be checked, and in case of agreements below 80%, all the films will be checked.

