#### Statistical analysis plans

Generalized estimating equation (GEE) with work matrix of first-order autoregressive factor will be used to the effects of the implementation of the intervention after the baseline assessment. Missing data will be treated as missing at a random mechanism via restricted maximum likelihood. The adopted significance level is 0.0125 (due to the four correlated outcomes, reducing the false discovery rates). For interobserver quality check, we will calculate the interobserver agreement using intraclass correlation (ICC) [55]. There are no plans to conduct additional analyses (e.g., subgroups or adjusted analyses).

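### The stated power of 75.84% uses a minimum phase length and an alpha that differ from the trial's own, and omits the number of students and the SD that scales d

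*Protocol article*

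**What the plan says.** All references are to the Protocol article.

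- **Sample size calculation and power.** The inputs are one baseline-intervention pair ("we have one baseline phase and one intervention phase"), intraclass correlation 0.5, autoregressive effect 0.5, alpha 0.016 because there are three primary outcomes, at least three observations per phase, and Cohen's d of 0.5. The result is "Under those input parameters, our power is 75.84" per cent. The section then notes that the intervention phase is longer than the baseline and concludes: "Therefore, our observable power will be superior than the above reported".
- **Design.** Forty students; "the shortest baseline has two assessments and the largest has five", and "the intervention phase has 18 assessments across time".
- **Statistical analysis plans.** A GEE with a first-order autoregressive working matrix. The level is set as follows: "The adopted significance level is 0.0125 (due to the four correlated outcomes, reducing the false discovery rates".
- **Primary outcomes** lists three tests and **Secondary outcomes** two. **Assessment of the outcomes** has films "evaluated by two external raters at item-level across the five primary outcomes", and **Video coding** repeats that count.

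**The concern.** A power figure describes a trial only if its inputs are those of the trial. Here two of them are contradicted elsewhere in the same article. One of the four randomised groups has fewer baseline observations than the assumed minimum, and the significance level is not the one adopted for the analysis. Behind the second mismatch lies an unsettled count of primary outcomes: three, four or five.

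Two further quantities are needed to get any power figure from this list: the number of students, and whether d is scaled by the total SD or by the within-student SD. Neither is among the inputs. With an intraclass correlation of 0.5 the choice of SD changes the effect by a factor of √0.5 ≈ 0.71, which matters more than either contradiction.

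This is the article's only power statement. As it stands, a reader cannot tell from it what effect the trial was able to detect.

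**Working it through.** **1. Inputs set side by side**

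| Input | Power section | Elsewhere in the article |
|---|---|---|
| Observations per phase | at least 3 | baseline 2 to 5; 18 in the intervention phase (Design) |
| Alpha | 0.016 | 0.0125 (Statistical analysis plans) |
| Outcomes behind alpha | 3 | 4 (Statistical analysis plans); 5 (Assessment of the outcomes, Video coding); 3 listed under Primary outcomes |
| Students | not listed | 40 (Design) |
| SD that scales d; one- or two-sided | not listed | not stated |

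0.05/3 = 0.0167 and 0.05/4 = 0.0125, so each alpha follows its own count.

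**2. Attempt to reproduce 75.84%**

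Assumptions: 40 students, two-sided test, an immediate and constant shift, and total variance 1 split into 0.5 between and 0.5 within students. Within-student errors are first-order autoregressive with coefficient 0.5.

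- Variance of a mean of three observations: 0.5 × 0.6111 = 0.3056.
- Covariance of the two adjacent phase means: 0.5 × 0.1701 = 0.0851.
- Variance of the phase difference per student: 2 × 0.3056 − 2 × 0.0851 = 0.441.
- Standard error with 40 students: √(0.441/40) = 0.105.

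Power at alpha 0.016:

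| Scaling of d | Shift | Noncentrality | t, 39 df | t, 78 df | Normal |
|---|---|---|---|---|---|
| Total SD | 0.5 | 4.76 | 98.5% | 98.8% | 99.1% |
| Within-student SD | 0.5 × √0.5 = 0.354 | 3.37 | 79.7% | 81.5% | 83.1% |

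Neither scaling returns 75.84%. One-sided versions are higher: 99.3–99.6% and 86.9–88.9%.

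**3. Cost of the two mismatches alone**

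The severe case gives every student two baseline and three intervention observations. The variance factor 0.8819 then becomes 0.9236, and the standard error √(0.5 × 0.9236/40) = 0.107. With t on 39 df:

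| | 3+3, alpha 0.016 | 2+3, alpha 0.0125 | Loss |
|---|---|---|---|
| Total SD | 98.5% | 97.5% | 1 point |
| Within-student SD | 79.7% | 74.6% | 5 points |

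**4. The claim that actual power is higher**

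Real layout: baselines of 2, 3, 4 and 5 (ten students each assumed) plus 18 intervention assessments, at alpha 0.0125.

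The simple difference of phase means (t, 39 df) gives 99.7% (total SD) or 88.5% (within-student SD). Both exceed the 3+3 values at the same alpha, 98.1% and 76.9%. For the before/after contrast the longer intervention phase does raise power.

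If calendar month enters the model (generalised least squares, normal reference), the result depends on its form:

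| Month term | Standard error | Total SD | Within-student SD |
|---|---|---|---|
| Linear | 0.099 | 99.5% | 86% |
| Categorical | 0.134 | 89% | 55% |

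The Primary outcomes section can be read as 18 assessments in all. On that reading linear month gives 99.1% or 83%, and categorical month stays at 89% or 55%.

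**The case against.** The strongest reply is that the non-reproduction cannot be pressed. The article credits the figure to a cited single-case power method run in named software, and neither is shown. Sidedness and the scaling of d are not given either. On within-student SD the gap is only about 4 to 6 points with a t reference. Adding the sampling variance of d (d²/(2 × 39)) to that scaling gives about 77.0% (normal reference), roughly one point away. This stands: the failure to reproduce is conditional on unseen conventions.

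A second reply is that leaving out the student count is mere condensation, since 40 appears throughout the article. That stands in part. The omission would be minor by itself, but the section presents its list as the parameters that yield the figure, and 40 with those parameters does not yield it in the model used here.

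A reader might infer three stronger things that the documents do not support.

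- *That the figure was computed for about half the students.* On total SD, 75.84% corresponds to some 17 to 20 students, depending on the reference distribution. With 40 students it corresponds equally well to d of about 0.34. Nothing in the article says which number was entered.
- *That the trial has only 55% power.* This needs both categorical month and within-student scaling, and the analysis section states no month term.
- *That the claim of higher power is false.* It agrees with the model for the before/after contrast, and on total SD even categorical month leaves power above 75.84%.

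**Conclusion.** The contradictions are certain and need no modelling: three observations against a two-assessment baseline, and 0.016 against 0.0125, with primary outcomes counted as three, four and five. The stated 75.84% is therefore not the power of the planned design.

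The size is modest. The two mismatches cost about 1 point on total SD and about 5 on within-student SD, and this overstates them, because only one group has a two-assessment baseline. The unstated scaling of d matters more: about 98.5–99% against about 80–81% for the listed inputs with 40 students. These figures assume a two-sided test, a constant shift and first-order autoregressive errors.

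It is tempting to conclude that the trial is underpowered. The working points the other way for the before/after contrast: with the real layout at 0.0125, power is above 75.84% on either scaling. This is a moderate reporting correction and does not question the sample size.

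**What to change.** 1. Settle one count of primary outcomes and one alpha. Use them in Sample size calculation and power, Assessment of the outcomes, Primary outcomes, Statistical analysis plans and Video coding.
2. Recompute power by simulation for 40 students in four groups with 2, 3, 4 and 5 baseline assessments plus the intervention assessments, under the final GEE model and final alpha. Reconcile first whether 18 counts the intervention phase or the whole follow-up.
3. State the number of students, the sidedness and the SD that scales d, and replace 75.84% with the result.
4. Correct the three-observation minimum to match the Design section.
5. Limit the statement "Therefore, our observable power will be superior than the above reported" to the contrast for which the simulation shows it. If month enters the model, report power for the form used.

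Cost: a short simulation and one rewritten paragraph. Recruitment is complete, and no students, assessments or procedures change.

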### Setting of the study

The intervention will take place in 12 schools from five different municipalities in Viken county in Norway. The participants are both in special schools, ordinary schools, and reinforced departments within ordinary schools. The teachers, familiar with the student, will deliver the instructions to the student during the school day. Each student has their own teacher/special education teacher who are responsible for their educational training. All teachers will receive individual training in test procedures, explicit teaching, and the reading material. The teachers will also be trained on how to score the tests and each work session. The main researcher will also be available for questions and guidance throughout the entire period.

### Intervention description

#### Recruitment

To recruit students, lectures were held at 12 schools, both ordinary schools, special schools, and schools with reinforced departments. The lectures were held in the period August to December 2022. The lectures emphasized informing about the reading program and the reading material “Reading for All” and about implementation and criteria for the reading intervention. Teachers, who had students within the criteria, registered themselves on an interest list, which the headteacher at the school passed on to the researcher. All the teachers were sent information letters and consent forms which they in turn sent to the parents, and all parents can contact the researchers by phone or email at any point in time during and after the trial. The teachers received their own consent forms. The principals at the respective schools collected all the consent forms and put them in sealed envelopes. They were then collected by the researcher and placed in a locked filing cabinet. The teachers who participate in the study will not be linked to the individual student, which help to strengthen the anonymity of the participants. The teachers and parents were asked to fill in the MacArthur-Bates Communicative Development Inventories (CDI) to document the individual student’s communicative competence. In February 2023, the teachers received training regarding the assessments and material. Baseline started in week 10 of March for all students.

#### Inclusion criteria

The inclusion criteria are as follows:Ages 6–14 yearsDiagnosed with intellectual disabilities, confirmed by multidisciplinary assessments carried out by the child rehabilitation serviceDoes not have a functional speech, i.e., require augmentative and alternative communication (AAC) to understand and/or make oneself understoodMust use AAC as their primary form of communicationCannot follow ordinary curricula LK20 [33] but have their own education plan

#### Exclusion criteria

The exclusion criteria are as follows:Students with severe visual impairmentStudents with severe hearing impairmentStudents who are able to decode single words and syllablesStudents with severe physical disability preventing the student from being able to point to answers with their fingers, unless they can respond with eye pointing or signs

#### Criteria for discontinuing or modifying allocated intervention

There will be no special criteria set for discontinuing or modifying allocated interventions. Given this is a non-pharmacological trial where the intervention is based on an educational approach with reading skills as outcome, we do not have special criteria for discontinuing or modifying allocated intervention. The parents and students are free to terminate participation at any time during the intervention.

#### Relevant concomitant care and interventions that are permitted or prohibited during the trial

Implementing the reading intervention will not require alteration to usual care pathways. The reading intervention is a complementary practice to what is offered in the schools. It is important to point out that in Norway, there is no evidence-based reading program for students who require AAC.

### Intervention

#### The reading material

The reading material “Lesing for alle” is based on the research of ALL [3]. The purpose is to work systematically with the various components within phonological awareness skills (sound blending and phoneme segmentation), letter-sound correspondence, shared reading, recognition of sight words, and single-word decoding. All the instructional activities have been adapted, and oral/spoken responses are not required for the students. The students can use alternative methods, such as signs, pointing at symbols, or pointing with their eyes. Evidence-based teaching based on the following: direct and systematic instruction [14, 16], explicit instruction [4, 14, 16], scaffolding, immediate and corrective feedback, cumulative review, and practice are used [3].

The reading program operates with six essential components:*Sound blending*, i.e., ability to build words from individual sounds by blending or combining sounds in sequence ([3], p. 71). Light et al. [4] argued that sound blending skills are important in learning to decode new words.*Letter-sound correspondence*, knowledge of the sounds represented by each of the letters and the letters used to represent different speech sounds [3]. Early letter knowledge is one of the factors that most strongly predicts reading skills later [34]. Being able to associate letters with sounds quickly and sounds with letters will help students to read and write [14].*Phoneme segmentation* is about dividing a word into sounds, counting sounds, pronouncing each sound clearly and separately, and the ability to listen out and break down words into single sounds [35]. Carnine et al. [35], Hulme et al. [36], and NRP [14] referred to research that described that phonological awareness correlated strongly with the acquisition of skills in reading and spelling. Browder et al. [37] emphasized that students with intellectual disabilities benefited from teaching phonemic awareness, but it was important that the phonemes were visually presented in the form of letters and pictures, so they could respond without functional spoken language.*Recognition of sight words*, ability to read/recognize a word without sounding it out [3]. Both phonological reading and word recognition are necessary for acquiring reading skills, and reading interventions are most effective when combining sight words with teaching decoding [10].*Single-word decoding*, the ability to recognize letters in words, associate them with correct sounds, and pull them together to the word the letter sequence represents [38, 39]. Decoding depends on letter knowledge and phonological skills [40, 41]. Good letter knowledge is a prerequisite for understanding and mastering the alphabetic principle, based on sounds represented by graphemes consisting of one or more letters [4].*Shared reading* is about the ability to use acquired skills and skills under development. Once students have developed basic skills in decoding simple words, it is important to use these skills in the context of meaningful and fun reading experiences [3, 4]. Browder et al. [42] claimed that shared reading helped to promote early reading skills for students with intellectual disabilities and is of importance as ordinary reading aloud is not as effective as explicit instruction in shared reading for this population of students [43, 44].

Emphasis will also be placed on working with additional activities such as flash cards and working on conceptual learning of the words they encounter in the reading program. All teachers get an overview of all the words that belong to the various levels in the reading material. It will be important to ensure basic comprehension skills on word level.

#### Design of the material

The tasks in sound blending, letter-sound correspondence, phoneme segmentation, sight words, and decoding are divided into four rectangular squares with a black frame in an A4 format. There is a symbol, letter, or word in each square. There is a corresponding instruction on each back of the assignment. The instructions lay down guidelines for what the teacher should say and how. The correct answer, target sound, or target word is marked in green so that the teachers can see what is correct. The instructions are short to adapt to the amount of verbal instruction the students can handle. Words and letters are written in small letters, with the font Arial, and the font size varies according to the different tasks. The tasks in “Shared reading” are made with images taken from the ALL App [45]. Through levels 1, 2, and 3, students encounter many words and symbols, about 350. The words are taken from McArthur-Bates Communicative development Inventory [46]. The entire material is made in the program InPrint and consists of Wigdit symbols [47]. Wigdit symbols are an English symbol layout that was created to support the reading and writing development of children who had difficulty cracking the reading code [48].

The material contains the following:*Level 0*. One folder (with about 60 tasks in explicit instruction in sound blending, letter-sound correspondence, shared reading, phoneme segmentation, sight words, and single-word decoding). Explicit instruction involves the teacher specifically identifying the skills for students to be taught in the lesson and then directly modeling the skill [49]. The current intervention will make use of explicit instruction through progressive scaffolding, which allows for systematically modeling of the concept, guided practice, and eventually to independence.

During the first step, the teacher is modeling for the student what will be required of them in each task and the student is a passive observer. The only expectation of them is that they are paying attention to the teacher. The teachers must follow the various scripts in the various reading components. The first step in the task is for the teacher to name all the four symbols and say “I’m going to say a word, listen to the word.” The teacher says the target word (for example seal). “Ssseeeaaalll,” the teacher says the word gradually faster, “sseeaall,” and finally say it normally, “seal.” Then, the teacher says “now I look at the symbols” and choose the symbol for “ssseeeaaalll.” The teacher points to the symbol for seal and at the same time says “ssseeeaaall” is a seal.”

During the second step, guided practice, the student is expected to be active in the lesson and is encouraged to point to the target item as well. In this step, the students get support to complete the tasks correctly together with the teacher. The teacher starts by saying “let’s do the task together.” It is the same script as in the modeling phase, but the teacher encourages the student to do it together.

During the final step, independent practice, students must perform independently. Teacher emphasizes and says “now it’s your turn, tap the glue icon.” If the student points to the correct symbol, the teacher says “good, g-llluuueee is glue.” The teacher points and confirms that the student has chosen the correct symbol. If the student answers incorrectly, the teacher corrects immediately and says “You pointed to xx (wrong answer), we have to find glue.”*Level 1*. Eight folders (with about 120 tasks in sound blending, letter-sound correspondence, and shared reading in each folder)*Level 2*. Thirteen folders (with about 120 tasks in sound blending, letter-sound correspondence, phoneme segmentation, single-word decoding, and shared reading in each folder)*Level 3*. Ten folders (with about 150 tasks in sound blending, letter-sound correspondence, phoneme segmentation, sight words, single-word decoding, advanced word decoding (for example, words with multiple consonant accumulations), not phonetic word pictures, recognition of high-frequency words, and shared reading in each folder)

There are clear instructions on the back of each task, so the training is carried out in the same way regardless of who is teaching the task. This also helps to create structure and predictability for the students. At the same time, the material is adapted so each student can use their alternative forms of communication. It is a goal that the students will receive instructions daily for about 30 min. The intervention will take place for a minimum of 1 year. The teachers must register each work session in registration forms. The forms are designed so that the teachers can select options 1, 2, 3, or 4, depending on how the student responds. The teachers must also register the time used with each work session and whether the student worked with explicit instructions or the reading tasks.

